### Intervention

We adapted the existing, evidence based internet version of PST, for use in pregnant women
[25]. We added psychoeducation on pregnancy and affective symptoms and adjusted the example patients in the programs. We named the intervention ‘MamaKits online’. The core assumption of PST is that affective symptoms are generated when people become overwhelmed by practical problems they face in their daily lives. When people are able to make a list of their worries and problems, and learn structured ways to resolve them, they feel less overwhelmed. Then they are better able to cope and this will in turn alleviate their mood
[19].

The course takes 6 weeks to complete, with one lesson each week. Each lesson consists of: information, examples and homework assignments. The intervention consists of three steps: (1) participants describe what really matters to them (2) participants write down their current worries and problems and categorize them into three types: (a) unimportant problems (problems unrelated to the things that matter to them), (b) problems which can be solved, and (c) problems which cannot be solved (e.g. the loss of a loved one), (3) participants make a plan for the future in which they describe how they will try to accomplish those things that matter most to them.

The core of the intervention consists of a structured approach to solve potentially solvable problems. It consists of six steps: (1) write a clear definition of the problem, (2) generate multiple solutions to the problem, (3) select the best solution, (4) work out a systematic plan for this solution, (5) carry out the solution, and (6) evaluate as to whether the solution has resolved the problem.

Trained coaches will give weekly feedback on the assignments through e-mail. The coaches will be master level psychology students, psychologists and psychiatrists who will receive a three hour training by an experienced PST therapist and are afterwards closely supervised by the same person. Based on previous experience with e-mail coaching we expect the coaching to take 15–30 minutes per participant per lesson. Feedback is aimed at supporting participants to work through the intervention and assignments, not to develop a therapeutic relationship. The main researcher, an experienced psychiatrist (HH), will check the integrity of the feedback.

### Control group

Participants in the control group are allowed to use ‘treatment as usual’ when needed. The ‘treatment as usual’ will be assessed through patients self-report by means of the questionnaires. Six weeks postpartum they will be offered the intervention.

### Instruments

#### Primary outcomes

**Depressive symptoms** We will use the Dutch version of the CES-D to measure symptoms of depression
[20]. This questionnaire has 20 self-rated items, each scored 0–3. The total score range is 0 (no depressive symptoms) to 60 (high number of depressive symptoms). The validity has been tested in different populations. Scores of 16 and higher represent a clinically significant level of depressive symptoms with a sensitivity of 0.82-1.00 and a specificity of 0.69-0.88
[26, 27] and is chosen as an inclusion criterion.

### Suicidality

We will use one question of the WSQ
[28] to asses suicidality. We will contact participants with a score 3 by telephone to give them advice about obtaining additional treatment. If needed we will also contact their general practitioner. For that reason we will also ask the telephone number of the participant and the name of het general practitioner.

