**Flowchart selection, inclusion, intervention and measurement.**

### Inclusion and exclusion criteria

We will include participants who are at risk for developing postpartum depression. More specifically, we will include participants of 18 years and older, who are pregnant but are at least 10 weeks before the expected delivery date, and have at least mild symptoms of depression or anxiety. Symptoms of depression are measured with the Center for Epidemiological Studies Depression scale (CES-D) and symptoms of anxiety with the Hospital Anxiety and Depression Scale- Anxiety subscale (HADS-A)
[20, 21]. Patients are eligible if they score at least 16 on the CESD and/or 8 on the HADS-A. Participants who indicate that they either intend to harm themselves or want to attempt suicide (as assessed by one question of the Web Screening Questionnaire (WSQ)
[22]) will be excluded. They are advised to consult their general practitioner to obtain more tailored care. Receiving psychiatric treatment including psychotherapy or the use of psychopharmacological agents such as antidepressants is allowed. Any additional treatments will be monitored through patients self-report at the end of study.

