### Recruitment

Participants will be recruited from the general Dutch population by means of banners on internet websites and advertisements in newspapers and magazines for pregnant women. These banners and advertisements refer to our study website. The website provides general information about the study and women can register online. All registered women will then be informed in more detail. They will also receive an informed consent form and a link to a baseline questionnaire. Only women who return a signed informed consent, complete the online baseline questionnaire, meet inclusion criteria and do not meet exclusion criteria will be included and randomized. Participants with very severe depressive or anxiety symptoms (CESD ≥ 25 or HADS-A ≥ 12) will be advised to contact their general practitioner as well, since the possibility exists that they need additional treatment. They will not be excluded since there exists evidence that the intervention is also helpful in case of severe depressive symptoms
[23, 24].

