### Assessments

All assessments are based on self-report and will take place online (Table 
1). We will measure at baseline (T0), 10 weeks later (although it is possible to finish the intervention in 6 weeks we know that there will be some people who need more time. To ensure that the post-test assessment takes place after completing the intervention we will perform the post-test assessments after 10 weeks.), when the intervention group has finished the intervention (T1), 4 weeks before the expected day of birth (in order to registrate symptoms of relapse (T2), and 6 weeks after delivery (T3). Participants starting the intervention after 24 weeks of pregnancy will not be assessed at T2, since the time period between T1 and T2 will be too small.

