**Table 1 Tab1:** **Assessment time table**

	T0	T1	T2	T3
CES-D	X	X	X	X
HADS	X	X	X	X
WSQ	X			X
EPDS	X	X	X	X
TiC-P	X	X	X	X
Euroqol	X	X	X	X
Demographic variables	X			
Delivery outcome				X

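### The suicidality question is scheduled only at baseline and 6 weeks postpartum, so randomised women have no scheduled trigger for the safety call in between

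*Protocol article*

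**What the plan says.** The Suicidality section of the protocol article uses a single WSQ question and attaches an action to it: "We will contact participants with a score 3 by telephone to give them advice about obtaining additional treatment". General practitioners may also be contacted, and telephone numbers and general practitioner names are collected for this purpose.

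In Table 1 the WSQ row is marked at T0 and T3 and blank at T1 and T2. The CES-D, HADS, EPDS, TiC-P and Euroqol rows are marked at all four times.

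Under Inclusion and exclusion criteria, women who "either intend to harm themselves or want to attempt suicide" according to the WSQ question are excluded, and "They are advised to consult their general practitioner to obtain more tailored care". Entry is open to women who are "at least 10 weeks before the expected delivery date", with no earliest week given. Under Recruitment, women with CES-D of 25 or more or HADS-A of 12 or more are told to contact their general practitioner, but "They will not be excluded since there exists evidence that the intervention is also helpful in case of severe depressive symptoms".

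The Assessments section puts T1 at 10 weeks after baseline, T2 at 4 weeks before the due date and T3 at 6 weeks after delivery. It adds that "Participants starting the intervention after 24 weeks of pregnancy will not be assessed at T2".

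**The concern.** The T0 answer works as an entry filter. Because reported intent at T0 keeps a woman out of the trial, T0 cannot pick up intent that starts after randomisation. The next scheduled WSQ question is at T3, the last assessment. In effect, the call procedure has one scheduled trigger for randomised women, and it comes at the end of follow-up.

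This matters because of who is enrolled. The trial seeks women at risk of postpartum depression, knowingly keeps those with very severe scores, and offers the control arm the intervention only after T3. Online batteries already go out in the interval, so the occasion to ask exists and is not used. What is at stake is participant safety; no estimate or test is affected.

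**Working it through.** **1. Schedule.** Reading Table 1 across T0, T1, T2, T3:

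| Row | T0 | T1 | T2 | T3 |
|---|---|---|---|---|
| WSQ | X | – | – | X |
| CES-D, HADS, EPDS, TiC-P, Euroqol | X | X | X | X |
| Demographics | X | – | – | – |
| Delivery outcome | – | – | – | X |

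The neighbouring rows make sense in this layout, so a broken table is an unlikely explanation for the two blanks.

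**2. Other triggers.** The article ties no CES-D, HADS or EPDS score at T1 or T2 to a call. The general practitioner advice for very severe scores is described at recruitment only. Coaches give weekly e-mail feedback and "are afterwards closely supervised by the same person", with a psychiatrist checking the feedback. That covers the intervention arm during the course, and the article states no escalation rule.

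**3. Current gap.** Let g be the gestational week at T0 and d the week of delivery. Then T1 = g + 10; T2 = 40 − 4 = 36, only if g ≤ 24; T3 = d + 6. The latest entry is week 40 − 10 = 30. The gap between WSQ checks is (d + 6) − g. The values of g and d are assumptions chosen to span the permitted range from week 20 onwards.

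| Entry week g | d = 37 | d = 40 | d = 42 |
|---|---|---|---|
| 20 | 23 | 26 | 28 |
| 24 | 19 | 22 | 24 |
| 25 | 18 | 21 | 23 |
| 30 | 13 | 16 | 18 |

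Entry at week 12 with d = 40 would give 46 − 12 = 34 weeks.

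**4. Gap with the question added at T1 and T2.**

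| Entry week g | Check weeks, d = 40 | Longest gap, d = 40 | Longest gap, d = 42 (T3 at week 48) |
|---|---|---|---|
| 20 | 20, 30, 36, 46 | 10 | 48 − 36 = 12 |
| 24 | 24, 34, 36, 46 | 10 | 48 − 36 = 12 |
| 25 | 25, 35, 46 | 11 | 48 − 35 = 13 |
| 30 | 30, 40, 46 | 10 | 10 |

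For entry at week 12 and d = 40, the checks fall at weeks 12, 22, 36 and 46, so the longest gap is 36 − 22 = 14 weeks, against 34 now.

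**5. Workload.** The planned 143 per arm reproduces: the t-test calculation for d = 0.40, two-sided alpha 0.05 and power 0.80 gives 99.08, rounded up to 100, and 100 / 0.70 = 142.9. Of 2 × 143 = 286 women, 286 × 0.70 ≈ 200 remain after the planned 30% attrition. The article gives no rate of new score-3 answers. Assuming 0.5% to 3% per wave:

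- Low: 200 × 0.005 = 1 call
- High: 200 × 0.03 = 6 calls

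This is for T1. T2 gives at most as many, since women starting after week 24 skip it.

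**The case against.** The strongest reply is that nothing here is an error. The sections agree with one another, the article does not claim to monitor suicidality throughout, and an article condenses a full protocol that an ethics committee approved. Rules for coach escalation, high follow-up scores or adverse events may well be in that protocol. Several safeguards are stated: exclusion with referral at T0, general practitioner advice for very severe scores, concurrent care including psychiatric treatment in both arms, and coaching in the intervention arm.

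Much of this is fair, and it limits the point. No claim can be made that the full protocol lacks other safety procedures. But the WSQ timing is not left unsaid: Table 1 fixes it, and it can be judged as fixed. None of the stated safeguards repeats the question after T0, and the control arm has no coach.

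Four narrower objections also carry some weight:

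- The exclusion criterion gives no score and the Suicidality section does not define a score of 3. Treating score 3 as reported intent is an inference.
- The 0.5% to 3% rate has no basis in the document, so the call count only indicates scale.
- Ten-weekly self-report still misses intent that arises between waves, and the gain is small for entry near week 30, where T1 falls around the due date.
- An action rule on CES-D or EPDS data already collected at T1 and T2 would be another route. It would need a new threshold, whereas the WSQ question already has one.

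**Conclusion.** The point holds. As scheduled, the WSQ question gives randomised women in both arms no trigger for the telephone call between T0 and T3. With delivery at week 40 that is 16 weeks at the latest permitted entry and 26 weeks for entry at week 20; across deliveries at weeks 37 to 42 the range for these entry weeks is 13 to 28. Earlier entry lengthens it.

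These figures rest on assumed entry and delivery weeks and on treating a score of 3 as the intent the exclusion criterion describes. The frequency of new-onset intent is unknown, so the number of women who would benefit cannot be stated. The change is advisable on safety grounds because it costs little. Sample size, estimand and analysis stay as they are.

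**What to change.** Mark the WSQ question at T1 and T2 in Table 1 for both arms, with T1 only for women starting after week 24. State that answers at these waves are reviewed promptly on receipt and that any score of 3 leads to the call already described in the Suicidality section. It would also help to say there what a score of 3 means. The content of the advice remains for the sponsor to decide.

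Women entering by week 24 gain two checks, T1 by week 34 and T2 at week 36. Later entrants gain one, between weeks 35 and 40.

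The questionnaire cost is one item in batteries already sent, and the contact details are already held. The real cost is staff time to review answers soon after they arrive: up to 286 at T1, about 200 after 30% attrition, and fewer at T2. The resulting calls would number about 1 to 6 at T1 under the assumed rate, and no more than that at T2.

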### Anxiety symptoms

For assessing anxiety symptoms the Dutch version of the HADS A is used. This is a 7 item anxiety subscale of the HADS with item responses on a 0 to 3 scale. Total score range is 0–21. Higher scores indicate more anxiety. The questionnaire is found to be reliable in the paper-pencil version
[29] as well as in the internet version
[30]. The HADS A has an optimal cut-off ≥ 8 with a sensitivity of 0.89 and a specificity of 0.75
[27].

### Perinatal outcomes

At 6 weeks after delivery we will assess the perinatal complications such as preterm birth (birth of baby less than 37 weeks gestational age), low birth weight, breastfeeding initiation and obstetric complications such as unplanned Caesarean Section, a vacuum extraction or longer duration of hospitalisation. This information will be obtained from participants only.

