## Abstract

**Background:**

Women in pregnancy and postpartum have an increased vulnerability to develop an affective disorder. Affective disorders in pregnancy are associated with an increased risk of prematurity, dysmaturity (foetal weight below the 10^th^ percentile as determined by ultrasound) and the development of postpartum depressive disorder. Untreated affective disorders and their complications may also result in considerable costs. Recent meta-analyses showed that interventions during pregnancy are less effective than postpartum interventions probably because of high attrition due to the barriers pregnant women experience with attending sessions outside their homes. An internet-based self-help intervention may overcome these barriers as it can be followed at home, and also in one’s own time. Such internet interventions showed to be effective for decreasing affective symptoms in general.

This randomised clinical trial examines whether an internet-based self-help intervention is effective in the reduction of affective symptoms in pregnancy and postpartum and results in an improvement of the perinatal outcome. We will also determine the cost-effectiveness of the intervention.

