In recent years self-help internet programs have become increasingly popular in mental health care. They are based on evidence based psychological treatments. Nowadays, numerous randomised controlled trials are available demonstrating the effectiveness of internet-based self-help interventions for different mental disorders such as depression
[12, 13], anxiety
[14, 15], alcohol
[16], and insomnia
[17]. Various treatment modalities have been applied within these trials, for example Cognitive Behavioural Therapy (CBT) and Problem-Solving Therapy (PST). It has been demonstrated that internet self-help treatments provided with support are more effective than those without any support
[18]. To our best knowledge no evidence is available on self-help internet interventions for depressive and anxiety symptoms in pregnancy.

We will examine the effectiveness of an intervention based on an existing, evidence based internet self help version of PST
[19] compared to a waiting list control condition on (1) the reduction of depressive and anxiety symptoms post intervention, end of pregnancy and 6 weeks postpartum and, (2) the improvement in perinatal outcomes (for example pre-term birth, growth restriction and breastfeeding initiation). We will also (3) determine cost-effectiveness using a societal perspective. We will further explain the intervention in the method section.

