## Discussion

The aim of this study is to investigate the effectiveness of an internet-based self-help intervention on depressive and anxiety symptoms in pregnancy. Furthermore we investigate the effects on pregnancy outcome. Through a calculation of costs and quality of life gains an indication can be given on the cost effectiveness of the intervention. This study has several limitations.

First not all women have access to the internet. This might be especially true for those with increased vulnerability for affective symptomatology during pregnancy such as social disadvantaged women in particular those with illiteracy, low educational level and low income. However especially in Western countries internet is broadly available and therefore this intervention is widely accessible during pregnancy.

Second, drop out rate may be high in the non intervention group due to lack of motivation. In order to counter this, therapy is offered at a later stage, 6 weeks post delivery.

A third limitation is the use of self rating instruments only. However since this intervention is aimed at affective symptoms and not at affective disorders a formal diagnosis seems not necessary.

The strength of the study is that we examine a short practical intervention for a specific group with mild to severe affective symptoms, which has proven to be (cost) effective in other populations. The broad inclusion and the use of the internet will allow us to create a high external validity. Furthermore the study is not only aimed at depressive, but also at anxiety symptoms, which is a common, but often neglected symptom in pregnancy and postpartum.

In case effectiveness is proven we will be able to offer an effective treatment of affective symptoms in pregnancy and their complications, reach many women and making therapy easier accessible.

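### Growth restriction is an aim, but the only size outcome named is low birth weight, not weight for gestational age; as a once-only self-report it is also lost for T3 non-responders

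*Protocol article*

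**What the plan says.** All references are to the protocol article.

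- **Status.** The Abstract (Methods/design) makes the perinatal outcome primary, alongside affective symptoms.
- **Aim.** The last paragraph of the Background gives the second aim as "the improvement in perinatal outcomes (for example pre-term birth, growth restriction and breastfeeding initiation". Growth restriction stands there as an item separate from pre-term birth.
- **Measure.** The Perinatal outcomes section lists "preterm birth (birth of baby less than 37 weeks gestational age), low birth weight, breastfeeding initiation", followed by obstetric complications. Preterm birth has a cut-off in weeks. Low birth weight has no cut-off and no reference to gestational age.
- **Timing and source.** The same section says "At 6 weeks after delivery we will assess the perinatal complications" and "This information will be obtained from participants only". Table 1 marks delivery outcome at T3 only.
- **Attrition and model.** Sample size and statistical analysis assumes 30% attrition. It specifies linear mixed models, chosen because they allow for dropout, with depression and anxiety symptoms as the dependent variables.
- **Dropout by arm.** The Discussion says "drop out rate may be high in the non intervention group due to lack of motivation", and names later access to the intervention as the countermeasure.

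**The concern.** Two of the three examples in the aim, preterm birth and breastfeeding initiation, carry over to the outcome list unchanged. The third does not: low birth weight stands where growth restriction stood. Growth restriction concerns size relative to gestational age, and a weight outcome that ignores gestational age measures something else. A baby small for its age but born at term can lie above a fixed weight limit and not be counted. A normally grown preterm baby can lie below the limit and be counted under both items. An effect, or its absence, on low birth weight would therefore not speak clearly to the stated aim.

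The second part concerns completeness. A birth outcome asked about once, of the mother only, has no other source if she does not answer T3. If the women who do not answer differ in risk from those who do, and the arms lose different proportions, the comparison of a primary outcome is biased.

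**Working it through.** **1. The plan's own figure.** Inputs from Sample size and statistical analysis: d = 0.40, two-sided alpha 0.05, power 0.80, attrition 30%. By the normal approximation, n = 2(1.96 + 0.842)² / 0.40² ≈ 98.1, so 99 per arm, and 99 / 0.70 = 141.4, so 142. By the t-test, n = 99.08, so 100 per arm, and 100 / 0.70 = 142.9, so 143. The stated 143 per arm is reproduced and is not in dispute. It is a calculation for symptom scores.

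**2. Women without birth data.** If the 30% applies at T3, 0.70 × 143 ≈ 100 women per arm answer, and 0.30 × 286 ≈ 86 women in total supply no delivery outcome. A mixed model uses a woman's earlier scores to inform a missing later one. A delivery outcome has no earlier value, so that mechanism is not available here.

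**3. Overlap of low birth weight with preterm birth.** The document gives no rates, so these inputs are assumptions. Let q be the preterm rate, a the share of preterm babies with low birth weight, and b the same share among term babies. The share of low-birth-weight babies who are preterm is qa / [qa + (1 − q)b].

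- Low end: q = 0.05, a = 0.40, b = 0.05 gives 0.020 / (0.020 + 0.0475) = 30%.
- High end: q = 0.10, a = 0.60, b = 0.01 gives 0.060 / (0.060 + 0.009) = 87%.

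The overlap is real, but it may lie below or above half.

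**4. Possible bias (hypothetical).** Assume a true risk of 10% in both arms and non-responders at twice the responders' risk r. With a proportion m missing, (1 − m)r + m(2r) = 0.10, so r = 0.10 / (1 + m).

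| Missing | Observed risks | Ratio |
|---|---|---|
| 20% vs 40% | 8.3% vs 7.1% | 0.857 |
| 25% vs 35% | 8.0% vs 7.4% | 0.926 |

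Both pairs average the planned 30%. The arm with more loss shows the lower observed risk. If that is the control arm, controls look better than they are and a real benefit would be masked.

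For scale, the first row is a shift of 1.2 percentage points. With about 114 and 86 responders (0.80 × 143 and 0.60 × 143), its standard error is √(0.0833 × 0.9167 / 114 + 0.0714 × 0.9286 / 86) ≈ 3.8 points, so the bias is about a third of one standard error.

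**The case against.** The case against has several good parts.

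- **The lists are open.** Both the aim and the outcome list are introduced as examples, and a condensed article may leave cut-offs to a fuller document. Preterm birth and low birth weight already call for gestational age and weight in some form, so a percentile may be derivable. This stands to the extent that one should not say the trial cannot answer the growth question. It does not remove the mismatch: the one size outcome the article names is not the one its aim names.
- **Low birth weight largely repeats prematurity.** A reader might infer this, but the document gives no figure, and the assumed range of 30% to 87% does not establish it.
- **Ultrasound.** A reader might infer that a promised ultrasound measure is missing. The Abstract's explanation of "dysmaturity (foetal weight below the 10^th^ percentile as determined by ultrasound" describes a background risk. Neither the aim nor the outcome section undertakes to use ultrasound.
- **Differential dropout.** A reader might take the Discussion to predict unequal loss. It says only that control dropout may be high, offers a countermeasure, and the sample size uses one rate for both arms.
- **Bias in every perinatal comparison.** This does not follow. Unequal loss biases a comparison only where non-response is also related to that outcome. Nor does the document say that the perinatal analysis will be restricted to completers; it gives no perinatal model. Stopping the course is also not the same as failing to answer T3.
- **Size of the bias.** The inputs in the example are invented and the shift is small beside its standard error. Both points are fair; the example shows direction and mechanism only.

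**Conclusion.** The point holds in a limited form. In an outcome labelled primary, the aim names growth restriction and the only size measure named is low birth weight, which as named is not relative to gestational age. That rests on the text alone.

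The loss of birth data follows from the single T3 self-report. The figure of about 86 of 286 women assumes that the 30% attrition applies at T3. Bias is conditional on non-response being related to the birth outcome and differing by arm; heavier control loss among higher-risk women would hide a benefit rather than create one. The symptom outcomes and the sample size of 143 per arm are unaffected. The change is worth making because it is cheap and aligns a primary outcome with its aim.

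**What to change.** 1. In Perinatal outcomes, define the growth outcome as birth weight below the 10th percentile for gestational age and sex on a named reference chart, derived from the mother's T3 report of birth weight, gestational age at birth and infant sex. Low birth weight may stay as a descriptive item.
2. Send T3 non-responders a short birth form by e-mail, the channel already used to tell women their allocation. It should carry the items needed for the growth and preterm outcomes, and mode of delivery. The Suicidality section requests the telephone number for safety follow-up, so any use of it for this purpose should be covered by the consent.

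Cost: possibly one added item (infant sex, if it is not already asked), a reference chart and one extra reminder. This assumes that T3 records birth weight and gestational age as values, not only as categories; the article does not say.
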